### Suspension of protocol

The protocol may be suspended for the individual patient at the discretion of the attending anesthesiologist if the patient is to be intubated in the presence of acute respiratory failure. In case of severe respiratory discomfort with the assigned therapy, the protocol may be temporarily suspended. The protocol will be resumed promptly after resolution of symptoms. These patients will be analyzed according to their originally assigned groups on an intention-to-treat basis.

### Statistics

For this study, 2 × 110 patients are needed to detect a 50% relative difference in the primary outcome, at a two-sided α level of 0.05 and a statistical power of 90%, assuming a 40% rate of postoperative hypoxemia in the standard oxygen therapy group [4,5]. An interim analysis is planned after enrollment of the first 110 patients to review data relating to patient safety and quality of trial conduct using the Lan and DeMets method (East software, Cytel Inc., Cambridge, MA, USA). The data and monitoring safety committee will recommend stopping the trial if the continued conduct of the trial compromises patient safety (a between-group difference in serious adverse events is found).

Statistical analysis will be conducted on an intention-to-treat (ITT) basis. Unadjusted chi-square or Fisher’s exact test will be used for primary outcome analysis. Adjusted analysis will be performed with the use of robust random effects Poisson generalized linear regression (1) to take into account adjustment on possible confounding covariates selected according to clinical relevance and (2) to consider within and between center variability. All effect sizes will be presented with 95% confidence intervals. The chi-square test (or Fisher’s exact test as appropriate) will be used for secondary binary outcomes. Continuous variables will be compared with the use of the unpaired *t* test or the Mann–Whitney *U* test when appropriate. The Shapiro-Wilk test will be used to assess normality, and the Fisher-Snedecor test to assess homoscedasticity. Adjusted analyses will be performed using the same adjustment variables, described previously, in the linear regression model. The time-to-event curves should be calculated with the use of the Kaplan-Meier method. If the frequency of missing data is >5%, an additional analysis will be performed using the multiple imputation method (STATA command mi) [21]. Longitudinal analysis using mixed models will be used to take into account between and within subject variability. All analyses will be conducted with Stata statistical software, version 12 (StataCorp LP, College Station, TX, USA). A two-sided *P* value of less than 0.05 will be considered to indicate statistical significance.

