**Methods/design:**

The Optiflow for prevention of post-extubation hypoxemia after abdominal surgery (OPERA) trial is an investigator-initiated multicenter randomized controlled two-arm trial with assessor-blinded outcome assessment, randomizing 220 patients with intermediate to high risk of pulmonary complications after abdominal surgery to receive HFNC or conventional oxygen therapy following extubation, stratified by the presence of epidural analgesia and center. The primary outcome measure is the percentage of patients with postoperative hypoxemia one hour after tracheal extubation. Secondary outcome measures are postoperative pulmonary complications, need for noninvasive ventilation and intubation for respiratory failure.

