### Randomization

Randomization is performed using a dedicated centralized telephone system, accessible round the clock, and using a computer-generated allocation sequence. The randomization sequence is generated using random blocks and is stratified per center and according to the planned use or nonuse of postoperative epidural analgesia, which is a factor that may influence outcomes [17]. No blocking is applied to other trial factors.

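### Randomization is stratified by center and planned epidural, but the primary test ignores both: a minor loss of efficiency if the strata are prognostic, and the Fisher option falls below the stated 90% power

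*Protocol article*

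**What the plan says.** The Randomization section of the protocol article states that allocation is "stratified per center and according to the planned use or nonuse of postoperative epidural analgesia, which is a factor that may influence outcomes". The abstract gives the same two factors: "stratified by the presence of epidural analgesia and center". Three centers are expected (Duration and timeline), so there are six strata.

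For the primary outcome, the Statistics section states: "Unadjusted chi-square or Fisher’s exact test will be used for primary outcome analysis". An adjusted analysis follows, using a random-effects Poisson model with robust errors. Its two stated purposes are "to take into account adjustment on possible confounding covariates selected according to clinical relevance" and "to consider within and between center variability". Center is therefore handled in that model. Its covariates are not named, and epidural analgesia appears nowhere in the section.

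On size, the section says "2 × 110 patients are needed to detect a 50% relative difference in the primary outcome", at two-sided α 0.05 and 90% power, "assuming a 40% rate of postoperative hypoxemia in the standard oxygen therapy group". That is 40% versus 20%.

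**The concern.** Stratified allocation removes chance imbalance in the stratum factors. If those factors are prognostic, the difference between arms varies less than it would under simple randomization. An unadjusted chi-square test still computes its variance as if randomization had been simple, so its standard error is too large. The nominal 5% test then runs below 5%, and part of the precision gained by stratifying goes unused.

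The protocol gives its own ground for expecting this with epidural, since it stratifies on epidural as a factor that may affect outcomes. It then fixes a primary test that does not use it. This is a stated choice of test, so it is not a detail left to the analysis plan.

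The sentence also leaves open which of two tests is primary, and they do not have the same power at the planned sample size.

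**Working it through.** **1. The plan's own figure.** Inputs from the Statistics section: p₁ = 0.40, p₂ = 0.20, two-sided α = 0.05, power 90%. With pooled rate 0.30 and no continuity correction,

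n = [1.960·√(2·0.30·0.70) + 1.282·√(0.40·0.60 + 0.20·0.80)]² / 0.20²
= (1.270 + 0.811)² / 0.04 ≈ 108.2, so 109 per arm.

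The planned 110 is reproduced. Power at 110 per arm by the same formula is 90.5%. With a continuity correction, 119 per arm would be needed, so the sample size matches an uncorrected chi-square test.

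**2. Why the unadjusted test is conservative.** With pooled rate p̄ and stratum rates pₛ, under the null,

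p̄(1 − p̄) = average of pₛ(1 − pₛ) + variance of pₛ between strata.

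The chi-square test uses the whole left side. With arms balanced within strata, only the first term on the right contributes to the variance of the difference. The standard error is therefore overstated by the factor 1/√(1 − Var(pₛ)/[p̄(1 − p̄)]).

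Example (assumed): epidural share 40%, epidural odds ratio 3, no center differences, overall rate 40%. The stratum rates are then about 29.5% and 55.7%. The between-stratum variance is 0.40·0.60·0.262² ≈ 0.0164, and 0.0164/0.24 ≈ 0.068. The effective critical value is 1.960/√0.932 ≈ 2.03, which gives a type I error of about 4.2%.

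**3. Simulation.** 40,000 trials per scenario, 220 patients, six strata, compared with a Cochran-Mantel-Haenszel (CMH) test over center by epidural. The documents give no center sizes, epidural share, block size or stratum risks. Assumed: center shares 50/30/20%, epidural share 40% (50% in the last row), blocks of 4, and center log-odds of −d, 0 and +d. Overall rates are 40% versus 40% for type I error and 40% versus 20% for power.

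| Epidural odds ratio | d | Type I error, chi-square / CMH | Power, chi-square / CMH |
|---|---|---|---|
| 1 | 0 | 4.9% / 4.9% | 90.8% / 90.7% |
| 2 | 0 | 4.7% / 5.0% | 90.9% / 91.2% |
| 3 | 0 | 4.1% / 4.9% | 91.2% / 92.2% |
| 2 | 0.5 | 4.2% / 5.0% | 91.3% / 92.1% |
| 3 | 0.7 | 3.8% / 5.2% | 91.8% / 93.5% |
| 4 | 1.0 | 3.0% / 5.1% | 92.6% / 95.1% |

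The 4.1% for odds ratio 3 alone agrees with step 2. A further simulation with other assumed risk spreads showed the same pattern. For example, stratum risks of 25% to 60% gave type I error 4.4% versus 5.1% and power 89.9% versus 90.5%.

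**4. Fisher's exact test.** This needs no assumption about strata. Enumerating all outcomes at 110 per arm, with 40% versus 20%, gives power of 90.6% for chi-square and 87.9% for Fisher. With 40% in both arms, Fisher's true type I error is 3.4%. The smallest expected cell at the planned rates is 110·0.30 = 33, far above the usual threshold of 5.

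**The case against.** The strongest reply is that no planned power is lost. The target is 90%, and across the scenarios above the unadjusted chi-square runs from 89.9% to 92.6%. It rises as the strata become more prognostic in the table. The shortfall is only relative to a better test, and type I error is never inflated. This stands, and it is why the point is minor.

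The loss is also conditional. The protocol says only that epidural may influence outcomes; it does not say that it predicts hypoxemia at one hour. With an epidural odds ratio of 2 and no center differences, the cost is 0.3 points. The largest losses need strong stratum effects. This stands too.

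A reader might go further and infer four things that the document does not support:

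- That epidural is excluded from every analysis. It is not named, but the unnamed covariates of the adjusted model could include it, and an analysis plan that is not shown may list them.
- That center is ignored throughout. It enters the adjusted model.
- That center was chosen as a stratum because centers differ in risk. The Randomization section gives a reason for epidural only.
- That the reported confidence intervals will be too wide. The section does not say which model yields them, and interval width was not computed here.

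Finally, Fisher's lower power comes from discreteness and has nothing to do with stratification. That is correct, so it is a separate point. It still matters, because the sentence on the primary outcome names Fisher with no rule for when it applies.

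**Conclusion.** The primary test does not carry the randomization strata. If they are prognostic, the unadjusted chi-square has a true type I error of about 4.7% down to 3% and gives up about 0 to 2.5 points of power against a stratified test. These figures rest on assumed stratum effects, center sizes, epidural share and block size. If the strata are not prognostic, nothing is lost.

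It would be wrong to conclude that the primary test is invalid or that the trial is underpowered with it: the error is on the conservative side, and about 90% power is kept.

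The Fisher option is firmer, because it follows from the plan's own inputs alone: 87.9% power against a stated 90%. Overall this is a minor point of efficiency and consistency.

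**What to change.** - Make the primary test a Cochran-Mantel-Haenszel test over center by planned epidural (six strata), or a modified Poisson regression with fixed terms for both factors and robust standard errors.
- Use planned epidural as recorded at randomization, since that is the factor used for allocation.
- Report the stratified risk ratio and risk difference with 95% confidence intervals.
- Keep the unadjusted chi-square as a sensitivity analysis.
- Drop Fisher's exact test as an option for the primary outcome.

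The cost is a change of wording, made before unblinding. Both factors are already in the randomization system, and no extra patients or data are needed. If the strata turn out not to be prognostic, the stratified test costs practically nothing (90.7% versus 90.8% power in the first row of the table).

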### Duration and timeline

Patients from three French University Teaching Hospitals are expected to be included during a two-year inclusion period starting September 2013.

2013: Protocol, approvals from ethics committee, and trial tool development (CRF, randomization system).

2013 to 2014: Inclusion of patients.

2014: Cleaning and closure of the database. Data analyses and writing of the manuscript, and submission for publication.

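### The adjusted Poisson model makes center a random effect with only three centers; if its robust variance is also taken at center level, the adjusted confidence interval could be far too narrow

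*Protocol article*

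**What the plan says.** The Statistics section of the protocol article gives the primary outcome two analyses. The first is a simple test: "Unadjusted chi-square or Fisher’s exact test will be used for primary outcome analysis". The second is a regression: "Adjusted analysis will be performed with the use of robust random effects Poisson generalized linear regression". That regression has two stated purposes: to adjust for clinically chosen covariates, and "to consider within and between center variability". The second purpose makes center the unit of the random effect.

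The Duration and timeline section gives the number of levels of that effect: "Patients from three French University Teaching Hospitals are expected to be included". The Randomization section says the sequence is "stratified per center and according to the planned use or nonuse of postoperative epidural analgesia", so the treatments are compared within center.

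The article does not say whether the robust variance is computed over patients or over centers, and it gives no small-sample correction. It promises 95% confidence intervals for all effect sizes and uses a two-sided 0.05 threshold.

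**The concern.** A random center effect needs enough centers to estimate a variance. Three centers leave two degrees of freedom.

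The more serious question is what *robust* refers to. In a random-intercept model, patients of one center share the random effect, so the likelihood splits into independent pieces only by center. A sandwich variance built on that likelihood adds up three terms. Referring the resulting statistic to the normal distribution treats three terms as if they were many.

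At stake are the interval and P value of the adjusted risk ratio. A null or borderline chi-square result could stand beside an adjusted result that is significant only because its standard error is unreliable.

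**Working it through.** **Inputs from the article.** Three centers; allocation within center; 110 per arm; 40% hypoxemia under standard oxygen and a 50% relative difference, hence 40% against 20%; two-sided 0.05; 90% power.

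**Assumptions not in the article.** Center sizes; a between-center SD of 0 or 0.5 on the logit scale; a null event rate of 40% or 20%; no covariates other than treatment and center.

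**1. The plan's own figure.** With pooled variance under the null, n per arm = [1.96·√(2·0.3·0.7) + 1.2816·√(0.4·0.6 + 0.2·0.8)]² / 0.2² = (1.270 + 0.811)² / 0.04 ≈ 108.2, so 109. Power at 110 per arm is 0.905. The stated 110 per arm is reproduced, and it does not depend on the adjusted model.

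**2. Variance component.** On 2 degrees of freedom an idealised 95% interval for a variance runs from 2/7.378 = 0.27 to 2/0.0506 = 39.5 times the estimate. A random-intercept Poisson model was fitted by maximum likelihood to 600 simulated trials per setting (centers of 74, 74 and 72). The center SD was estimated at or near zero (below about 0.02 on the log scale) in 43% of trials when the true logit SD was 0.5, and in 90% when it was 0.

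**3. Center-level sandwich, by formula.** For t on 2 degrees of freedom, P(|T| > c) = 1 − c/√(2 + c²).
- With the factor G/(G−1) = 3/2 and c = 1.96: 1 − 1.96/√5.8416 = 18.9%.
- Without the factor, c becomes 1.96·√(2/3) = 1.600: 1 − 1.600/√4.561 = 25.1%.
- The critical value that gives 5% is 4.30, so the half-width should be 4.30/1.96 = 2.2 times as large.

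**4. Simulated false-positive rate at nominal 5%.** No treatment effect, 220 patients, three centers. Poisson log-link rows: 4,000 trials in each of eight settings (centers of 74/74/72 or 120/60/40, SD 0 or 0.5, event rate 40% or 20%). Random-intercept rows: the 600-trial runs of step 2, at a 40% event rate.

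| Method | Rate |
|---|---|
| Poisson, center-level sandwich, no factor | 23–28% |
| Poisson, center-level sandwich, with factor | 17–21% |
| Random-intercept Poisson, center-level sandwich, no factor | 25.5–26.5% |
| Random-intercept Poisson, center-level sandwich, with factor | 17.5–18.0% |
| Random-intercept Poisson, model-based SE | 1.2–1.3% |
| Poisson, patient-level robust SE | 3.9–5.5% |
| Fixed center effects, patient-level robust SE | 4.1–5.6% |
| Fixed center effects, center-level sandwich, with factor | 17–21% |
| Poisson, center-level sandwich, with factor, t on 2 df | 4.4–5.5% |
| Unadjusted chi-square | 4.0–6.0% |

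The Monte Carlo standard error is about 0.3 points near 5% with 4,000 trials and about 1.6 points near 18% with 600. A separate set of 20,000-trial simulations with other center sizes and risks gave 18.2–19.1% with the factor, 24.4–25.4% without, and 4.0–4.7% for patient-level robust errors.

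**5. Why the model-based rate is low.** Poisson variance p overstates binary variance p(1−p). At p = 0.4 the effective critical value is 1.96/√0.6 = 2.53, a size of about 1.1%. At p = 0.2 it is 1.96/√0.8 = 2.19, about 2.8%. A robust variance is therefore needed, and its level decides whether the test is valid.

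**6. Dependence on the number of centers.** The center-level sandwich with the factor gave 7.0% with 10 centers and 5.0% with 20.

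**The case against.** The strongest reply is that the article never says the variance is clustered on center. In a Poisson model for a binary outcome, *robust* may mean only the patient-level correction for the wrong variance, and then the size is near 5%. The level of the sandwich is also a detail that a condensed article may leave to the analysis plan. This stands in part: the inflation is conditional and must be stated so. It does not remove the point, because the article does fix a random center effect with three levels, and the usual sandwich for that likelihood is the center-level one.

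Four stronger readings are tempting, and the documents do not support them.
- **The adjusted P values will be too small.** One of three possible variance choices makes them so; the other two give about 5% or less.
- **The poor variance estimate shrinks the P values.** Treatment is allocated within center, and an estimate of zero merely drops the center effect from the model. Neither route produced inflation.
- **The primary result is at risk.** The primary test is the unadjusted chi-square or Fisher test, which does not use this model.
- **The adjusted secondary results share the problem.** For secondary binary outcomes the Statistics section names chi-square or Fisher tests. Its later sentence on adjusted analyses refers to linear regression with the same covariates and mentions neither a random center effect nor a robust variance.

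Fixed center effects are also not the only valid repair: a center-level sandwich referred to t on 2 degrees of freedom holds its size, though with a critical value of 4.30.

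**Conclusion.** The concern holds in conditional form. A random center effect is ill-suited to three centers, because its variance cannot be usefully estimated. Depending on a variance choice that the article leaves open, the adjusted test of the primary outcome has a true size of about 1%, about 4–5.5%, or about 17–28%. In the last case a nominal 95% interval covers about 72–83% of the time.

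These figures rest on three centers, which is the expected number, and on the assumed center sizes, event rates and between-center spread. The center-level figures moved little across those assumptions and agree with the closed-form 18.9% and 25.1%. The matter should be settled before the unblinded analysis, but it concerns a supporting analysis.

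**What to change.** Replace the model sentence along these lines: the adjusted analysis of the primary outcome, and of any other binary outcome analysed with this model, uses modified Poisson regression (log link) with treatment, center (two indicator terms), planned epidural analgesia and the prespecified covariates as fixed effects, and patient-level (Huber-White) robust standard errors.

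Both parts are needed. Fixed center effects with a center-level sandwich were still inflated (17–21%); with patient-level errors the size was 4.1–5.6%. The fixed terms also follow the two stratification factors.

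The cost is one sentence and three model terms (two for center, one for epidural) among 220 patients. The downside is that inference is limited to the participating centers, which is all that three centers can support.

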### Study endpoints

Primary outcome variable is the percentage of patients who developed postoperative hypoxemia one hour after tracheal extubation. Postoperative hypoxemia is defined as PaO_2_/FiO_2_ ratio <300, as used previously [11].

Secondary outcome variables are postoperative gas exchange one hour after extubation and after discontinuation of the allocated treatment, respiratory discomfort (using a numerical rating scale, ranging from 0 to 10), need for supplemental oxygen therapy (defined as arterial oxygen saturation <93% on room air), need for postoperative reintubation and/or NIV for acute respiratory failure within the first seven days after surgery, postoperative pulmonary complications within the first seven days after surgery, unexpected intensive care unit (ICU) admission or readmission, ICU and hospital length of stays, and in-hospital mortality. Acute respiratory failure is defined by one of the hypoxemic criteria (peripheral oxygen saturation (SpO_2_) <92% while breathing at least 10 L/min oxygen, PaO_2_ <60 mmHg on air or PaO_2_ <80 mmHg while breathing any supplemental oxygen) and at least one of the following criteria: severe respiratory distress with dyspnea, accessory muscle recruitment and paradoxical abdominal or thoracic motion, respiratory rate >25 breaths/min, respiratory acidosis with pH <7.30 and arterial carbon dioxide partial pressure (PaCO_2_) >50 mmHg [19]. Postoperative pulmonary complications are scored with the use of a graded scale [20] from 0 (no pulmonary complications) to 4 (the most severe complications). Postoperative pulmonary complications are defined as: atelectasis (opacification of the lung with shift of the mediastinum, hilum or hemidiaphragm toward the affected area and compensatory overinflation in the adjacent nonatelectatic lung); suspected pulmonary infection (patient receives antibiotics and meets at least one of the following criteria: new or changed sputum, new or changed lung opacities on chest X-ray when clinically indicated, tympanic temperature >38.3°C, white blood cell (WBC) count >12,000/μl in the absence of other infectious focus); pleural effusion (chest X-ray demonstrating blunting of the costophrenic angle, loss of the sharp silhouette of the ipsilateral hemidiaphragm in upright position, evidence of displacement of adjacent anatomical structures or (in supine position) a hazy opacity in one hemithorax with preserved vascular shadows); and pneumothorax (air in the pleural space with no vascular bed surrounding the visceral pleura).

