In conclusion, the OPERA trial is an investigator-initiated pragmatic randomized controlled trial powered to test the hypothesis that early application of HFNC prevents postoperative hypoxemia in patients with intermediate to high risk of postoperative pulmonary complications. The OPERA trial also determines the effects of high-flow oxygen therapy on most of the postoperative pulmonary complications, need for noninvasive mechanical ventilation or intubation for postoperative respiratory failure, and lengths of ICU and hospital stays.

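### One unrestricted P<0.05 rule spans ten unranked secondary outcomes, some of them worded as confirmatory, though only hypoxemia is powered (minor)

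*Protocol article*

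**What the plan says.** The plan names a single primary outcome: "Primary outcome variable is the percentage of patients who developed postoperative hypoxemia one hour after tracheal extubation". The sample size is built on it alone: "2 × 110 patients are needed to detect a 50% relative difference in the primary outcome", "assuming a 40% rate of postoperative hypoxemia in the standard oxygen therapy group".

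Study endpoints then gives the secondary list, which begins: "Secondary outcome variables are postoperative gas exchange one hour after extubation and after discontinuation of the allocated treatment, respiratory discomfort". It continues through supplemental oxygen, reintubation or NIV, pulmonary complications, ICU admission, two lengths of stay and mortality. The Abstract gives a shorter list: "Secondary outcome measures are postoperative pulmonary complications, need for noninvasive ventilation and intubation for respiratory failure". The Statistics section gives neither list an order or a priority.

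Statistics assigns chi-square or Fisher tests to binary secondaries and t or Mann–Whitney tests to continuous variables, adds adjusted analyses, and promises 95% confidence intervals for all effect sizes. It ends with the general rule: "A two-sided *P* value of less than 0.05 will be considered to indicate statistical significance".

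Four places describe what the trial can show beyond hypoxemia:

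- The Abstract's Discussion paragraph says the trial is powered to investigate prevention of hypoxemia and of pulmonary complications.
- The last paragraph of the Background states the aim as a comparison of effects on postoperative pulmonary complications.
- The last paragraph of the Discussion says: "The OPERA trial also determines the effects of high-flow oxygen therapy on most of the postoperative pulmonary complications", and extends this to NIV or intubation and to ICU and hospital stays.
- The second paragraph of the Discussion is more cautious. It says only that determining effects on other complications may be possible.

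**The concern.** A missing hierarchy for secondary outcomes would not by itself be a finding in a condensed article. The difficulty here is in what the article states. It fixes a decision rule that follows the description of primary, secondary and adjusted tests and is not restricted to any of them, and it uses confirmatory language for some of the secondary outcomes.

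Taken together, these passages would let a report call an isolated P<0.05 on pulmonary complications or length of stay a statistically significant effect of HFNC even if the primary comparison were null, and cite the protocol article in support. At stake is how much weight a secondary result can bear. The primary conclusion is not affected.

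**Working it through.** **Step 1. The plan's own figure.** Inputs from Statistics: control rate 0.40, relative reduction 50% (so 0.20 under HFNC), two-sided α 0.05, power 90%. With pooled variance under the null and mean rate 0.30:

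n = [1.96·√(2·0.30·0.70) + 1.2816·√(0.40·0.60 + 0.20·0.80)]² / 0.20²
= (1.270 + 0.811)² / 0.04 ≈ 108.2, so 109 per arm.

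The unpooled form gives 106. Power at 110 per arm is 90.5%. The stated 110 per arm reproduces, for hypoxemia only.

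**Step 2. Count the secondary outcomes in Study endpoints.**

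1. Gas exchange at one hour
2. Gas exchange after discontinuation
3. Respiratory discomfort
4. Supplemental oxygen
5. Reintubation and/or NIV by day 7
6. Pulmonary complications by day 7
7. Unexpected ICU admission or readmission
8. ICU stay
9. Hospital stay
10. In-hospital mortality

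The count of ten splits gas exchange by time point and counts the two lengths of stay separately.

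**Step 3. Chance of at least one P<0.05 if HFNC has no effect, independent tests.** The formula is 1 − 0.95^m.

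- Ten outcomes: 1 − 0.95^10 = 40.1%.
- Four outcomes named in the closing paragraph of the Discussion (complications, NIV or intubation, ICU stay, hospital stay): 1 − 0.95^4 = 18.5%.
- The Abstract's shorter list, counted as three: 1 − 0.95^3 = 14.3%.
- Ten outcomes, counting only false results in favour of HFNC: 1 − 0.975^10 = 22.4%.

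**Step 4. Allow for correlation.** The documents give no correlations, so these are assumptions. Ten equicorrelated normal statistics were simulated as Z_j = √ρ·C + √(1−ρ)·E_j with 200,000 replicates, taking the share with any |Z_j| > 1.96:

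| Assumed ρ | At least one P<0.05 |
|---|---|
| 0.1 | 39% |
| 0.3 | 35% |
| 0.5 | 29% |
| 0.7 | 21% |

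**Step 5. Discreteness of rare binary outcomes.** At 110 per arm, the true size of Fisher's exact test at nominal 0.05 is 0.6% for a 2% event rate and 2.3% for a 5% event rate. Rare outcomes tested this way add less than the formula in Step 3 assumes.

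**Step 6. What it would take to pass one half.** Thirteen independent tests give 1 − 0.95^13 = 48.7%, and fourteen give 1 − 0.95^14 = 51.2%. At an assumed correlation of 0.3, fourteen give 44%. Separate tests of blood-gas variables or adjusted re-analyses could raise the count, but the article does not list them as separate tests.

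**The case against.** The strongest reply is that this is a condensed article, that multiplicity across secondary outcomes is commonly left to a full protocol or SAP, and that the quoted rule is a generic closing line that rules out no hierarchy elsewhere. Much of that stands, and it is why the point is minor. It does not remove the point, because the unrestricted rule and the confirmatory wording are in the text, and the Discussion is itself inconsistent about how firm the secondary conclusions can be.

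Other parts of the reply stand in full:

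- A reader might infer that a false secondary claim is likely. The figures do not support this. Even ten independent tests give 40%, positive correlation lowers it, and several of these outcomes are clinically linked.
- A reader might infer that every secondary outcome will be declared significant or not, one by one. The article does not say so. That follows only from the general sentence.
- A reader might infer that all ten are presented as determined effects. The closing paragraph does not say this of gas exchange, discomfort, supplemental oxygen, unexpected ICU admission or mortality.
- A reader might infer that the risk is greatest for the clinical outcomes. The documents give no event rates for them, and Step 5 shows that Fisher's test on rare events falls below 5%.
- The article never promises a 5% error rate across the secondary family, so the figures describe what the rule allows. They do not show a broken promise.

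**Conclusion.** The point holds as a minor one. The article's significance rule is wider than its design supports, and the Abstract, the Background and the end of the Discussion present pulmonary complications (and, in the last case, NIV or intubation and lengths of stay) more firmly than a trial sized for hypoxemia allows. With no treatment effect, at least one nominally significant secondary result has a probability of up to about 40%, about 21% to 35% at correlations of 0.7 to 0.3, and 18.5% for the four outcomes in the Discussion's closing paragraph if independent. These figures rest on a count of ten outcomes, one test each, every test at its nominal size, and assumed equal correlations. The primary test and the 220-patient sample size are unaffected.

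**What to change.** 1. In Statistics, limit the closing significance sentence to the primary outcome.
2. State that all secondary outcomes and all adjusted re-analyses are exploratory and are reported as effect sizes with the 95% confidence intervals the section already promises, without a claim of significance.
3. In the Abstract, say that the trial is powered for hypoxemia only. In the last paragraph of the Discussion, replace the claim to determine secondary effects with one to explore them, in line with the cautious sentence earlier in that section.
4. Optional: if the sponsor wants a confirmatory secondary claim, specify before database lock a short fixed sequence after the primary, in an order of the sponsor's choosing. Each step is tested at two-sided 0.05 only if the primary and every earlier step were significant. This holds the error across the primary and the sequence at 5%. The Discussion may then keep firm wording for the outcomes in the sequence.

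The cost is a few sentences, with no new data and no more patients. The downside is that an isolated secondary P<0.05 can no longer be called significant, and any sequenced outcome can be claimed only if the primary succeeds. If the full protocol or SAP already contains a hierarchy, the only change needed is to align the article's wording with it.
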